### Waiting list group (no combination exercise training group)

The wait-listed group receives no intervention. Those participants are informed by letter that they are scheduled to receive an invitation to participate after a waiting period of four weeks. We ask the wait-list group not to go to the gym or not to join exercise programs during the waiting period. The previous study [35] suggested that the wait-listed group tends to show a resentful demoralization and to withdraw from the study. Based on this suggestion, 1) we set a short-term waiting duration (four weeks) and 2) to keep the motivation to participate in this study, we will send a short letter to the wait-list group at the midpoint of the waiting duration. In this study, we use no active control group such as a stretch exercise training group alone or placebo group such as a social contact group because results of previous intervention reports describe that no difference exists in cognitive or functional improvement between the stretch exercise training group (active control group) and non-exercise control group (control group) [36] or between the social-contact group (placebo group) and no-social-contact groups (control group) [37,38]. Moreover, using the wait-list control group has the advantage of letting everyone in the study receive the new intervention such as the combination exercise training (sooner or later). Thus, we use the wait-list control group in this intervention study.

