### Sample size

Our sample size estimation is based on the change score in the reverse Stroop task, which is the primary outcome in this study. This study uses eta squared (η^*2*^) as an index of effect size. As a descriptive index of strength of association between an experimental factor (main effect or interaction effect) and a dependent variable, η^*2*^ is defined as the proportion of total variation attributable to the factor, and it ranges in value from 0 to 1 [52]. Using information (the sums of squares for total; SS total, the sum of squares for factor; SS factor) reported in an analysis of covariance (ANCOVA) summary table, we calculate η^*2*^ (SS factor divided by SS total). SS factor is the variation attributable to the factor and SS total is the total variation, which includes the SS factor and the sum of squares for error. In actuality, η^*2*^ ≥0.01 is regarded as a small effect, η^2^ ≥0.06 as a medium effect, and η^*2*^ ≥0.14 as a large effect [52]. We expect to detect a large effect size (η^2^ = 0.14) of the change score (post-training score minus pre-training score) in the reverse Stroop task between combination exercise and waiting list groups. The sample size was determined using G*power [53,54] based on 80% power, a two-sided hypothesis test, an alpha level of 5%, an ANCOVA model that includes a baseline reverse Stroop task score, age and sex as a covariate. The sample size calculation indicated that we need 32 participants in each of the combination exercise and waiting list groups with consideration of a 20% drop-out rate.

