### Analysis

This study is designed to evaluate the beneficial effect of the short-term combination exercise in older people. We calculate the change score (post-training score minus pre-training score) in all cognitive function measures. We conduct an ANCOVA for the change scores in each cognitive test. The change scores are the dependent variable. Groups (combination exercise, waiting list) are the independent variable. Pre-training scores in the dependent variable, sex, age categories are covariates to adjust for background characteristics and to exclude the possibility that any pre-existing difference of measure between groups affects the result of each measure. The level of significance is set as *P* <0.05. This study reports η^*2*^ as an index of effect size (please see the detail in Sample Size). Missing data are imputed using Missing Value Analysis in the Statistical Package for the Social Sciences (SPSS). In particular, we impute missing values using maximum likelihood estimation based on the expectation-maximization algorism with the observed data in an iterative process [55]. All randomized participants are included in the analyses in line with their allocation, irrespective of how many sessions they complete (intention-to-treat principle). All analyses are performed using the SPSS (version 18 or higher; SPSS Japan Inc.).

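### Filling missing scores once by EM and analysing them as observed either raises the type I error to about 12% or shrinks the effect by about a fifth at the planned 20% drop-out, depending on an unspecified imputation model

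*Protocol article*

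**What the plan says.** The Analysis section of the protocol article sets the rule for missing data. Missing values are handled in SPSS Missing Value Analysis, and "we impute missing values using maximum likelihood estimation based on the expectation-maximization algorism with the observed data in an iterative process". The completed change scores go into an ANCOVA with group as the factor and the pre-training score, sex and age category as covariates, tested at 5%. On the analysis set it says: "All randomized participants are included in the analyses in line with their allocation". It gives no number of imputed data sets, no pooling rule, no added residual and no correction of standard errors or degrees of freedom. It does not say which variables enter the imputation model, or whether arms are imputed separately.

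The Sample size section arrives at 32 per group "with consideration of a 20% drop-out rate". The Waiting list group section cites an earlier study's suggestion that "the wait-listed group tends to show a resentful demoralization and to withdraw from the study", and describes a short wait and a midpoint letter as measures against this.

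**The concern.** EM can give valid estimates of means and covariances when data are missing at random. The difficulty lies in the step after it. A score filled in with its conditional expectation lies exactly on the imputation regression and carries no residual scatter. An ordinary ANCOVA on the completed file treats it as a measured score. The residual variance is then too small, and the degrees of freedom and the sample size behind the standard error are too large.

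If the imputation model leaves group out, the fault takes another form. Filled-in scores take the same predicted value in both arms, and the estimated group difference is pulled towards zero.

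The Stroop comparison and every secondary test use this method. What is at stake is either the P value and confidence interval, or the effect estimate, the interval and the η² that the trial intends to report.

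**Working it through.** **Inputs from the Sample size section.** The test is set out as "based on 80% power, a two-sided hypothesis test, an alpha level of 5"%. The effect is η² = 0.14. The model is "an ANCOVA model that includes a baseline reverse Stroop task score, age and sex as a covariate". With intercept and group, that makes 5 parameters. The sample is 32 per group, 64 in total, after allowing for 20% drop-out.

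**Assumptions (not in the documents).** One conditional-mean fill-in without random residuals; complete baseline data; post-scores missing completely at random. The simulations also assume a pre-post correlation of 0.7. The analytic check does not need it.

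**1. The plan's own figure.** f² = 0.14/0.86 = 0.163. With noncentrality f² × N and N − 5 error degrees of freedom, N = 51 gives power 0.805. Then 51/0.80 = 63.75, rounded up to 64, or 32 per group. The stated sample size reproduces and is not in question. It rests on 51 participants with data, so 64 − 51 = 13 are missing.

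**2. Group in the imputation model, or imputation by arm.** With complete covariates, the EM fill equals the regression prediction from the completers, so the group estimate stays unbiased. The residual sum of squares comes from 51 people with 51 − 5 = 46 degrees of freedom, but is divided by 64 − 5 = 59. The standard error is also computed as if 64 people contributed.

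- Ratio of reported to correct standard error: √((46/59) × (51/64)) = 0.788.
- The nominal critical value on 59 degrees of freedom is 2.001. The effective one is 0.788 × 2.001 = 1.577.
- Type I error: 2 × P(t₄₆ > 1.577) = 0.122. Interval coverage: 1 − 0.122 = 0.878.

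Simulation with 10,000 null data sets gave 12.2%. At the planned effect (a difference of 2 × √0.163 = 0.807 residual SD) the mean estimate was 0.808. Adding nine other baseline scores as predictors gave 11.8%. Unequal loss of 30% and 10% by arm gave 13.0%.

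**3. Group not in the imputation model.** About 51/64 = 0.80 of the group contrast survives, because filled-in scores carry none of it. In simulation the estimate fell from 0.807 to 0.633, a ratio of 0.78. Type I error was 5.2%, and power was the same as for the observed-data ANCOVA, about 77% in each. Interval coverage at the planned effect was 88 to 89%.

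**4. By amount missing.**

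| Missing | Type I error, group in model | Effect retained, group not in model |
|---|---|---|
| 5% (3) | 6.2% analytic, 6.7% simulated | 0.770/0.807 = 0.95 |
| 10% (6) | 7.7% by both | 0.729/0.807 = 0.90 |
| 20% (13) | 12.2% by both | 0.633/0.807 = 0.78 |

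**5. Without the fill-in.** The same ANCOVA on the 51 observed scores gave type I error 5.2% and a mean estimate of 0.808 against 0.807. Its simulated power of about 77% is below the formula's 80.5%, which assumes exact balance; the simulation used simple randomisation. Multiple imputation was not simulated.

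**The case against.** Four objections deserve weight.

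**The two faults are alternatives.** A reader might infer that type I error, interval and effect size all fail together, or that the trial simply runs at 12%. The protocol does not support that. It does not say whether group is in the imputation model. If group is left out, the primary test keeps its 5% level and loses no power against the observed-data analysis; the estimate is then conservative. This objection stands, and the 12% must be stated as conditional. It does not rescue the method, because the estimate and the interval are still wrong in that branch.

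**A single fill-in without residuals is inferred.** The text never says single and does not describe the residuals. That also stands as a condition. Still, EM followed by one ANCOVA, with no pooling step, is most naturally read this way.

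**20% is a planning allowance, not a forecast.** Missed exercise sessions do not by themselves make a score missing. With less loss the harm is smaller, as the table shows, but it does not vanish.

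**Wait-list withdrawal.** A reader might infer that the protocol expects demoralised wait-list participants to leave, so that selective loss would be hidden. The text reports what an earlier study suggested and sets out measures to prevent it. It shows only that the sponsor regards such withdrawal as plausible and tries to limit it. No calculation here relies on selective loss; both faults arise even when scores are missing completely at random.

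That the article condenses a fuller plan is no answer either. The imputation method is stated, and adding the list of imputation variables elsewhere would only decide which of the two faults applies.

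**Conclusion.** The point holds in conditional form. On the natural reading of the Analysis section, imputed scores are treated as measured ones. With 13 of 64 missing, the result is one of the following:

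- **Group in the imputation model, or imputation by arm:** unbiased effect, standard error about 0.79 of the correct value, type I error about 12%, coverage about 88%.
- **Group left out:** type I error near 5%, effect shrunk by about a fifth, coverage about 88% at the planned effect.

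Neither branch reports both the effect and its uncertainty correctly. At 5 to 10% missing, the type I error is about 6 to 8%, or the shrinkage about 5 to 10%. The conclusion rests on one conditional-mean fill-in and, for the sizes, on complete baseline data and random loss. The 12% itself follows from sample counts and degrees of freedom alone. The sample size of 64 is sound.

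**What to change.** Replace the EM fill-in in the Analysis section with one of two methods.

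- **(a) Likelihood on observed scores.** Fit the same ANCOVA to the observed scores, by allocated group. Participants without a post-training score then contribute no outcome, so the sentence that includes every randomised participant must be amended to match.
- **(b) Multiple imputation.** Impute with group in the model (or separately by arm), together with pre-training scores, age and sex, and combine the analyses by Rubin's rules. This keeps all 64 in the analysis.

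If (b) is chosen, a sensitivity analysis that shifts the imputed values by arm can be added to probe the missing-at-random assumption. It is optional, and it does not apply to (a), which has no imputed values.

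The cost is analysis wording only; no extra participants or assessments are needed. P values will be less favourable than under a fill-in with group in the model. Against a fill-in without group, option (a) left the simulated rejection rates essentially unchanged and removed the shrinkage. The Trial status section says recruitment is still under way, so the change can be made before outcome data are analysed.

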## Discussion

This study is designed to investigate the beneficial effects of short-term combination exercise training on diverse cognitive functions such as executive functions, episodic memory, short-term memory, working memory, reading ability, attention, and processing speed in healthy older people.

This study has several strengths compared to earlier studies using exercise training for older people. First, we use hydraulic exercise machines to increase muscle strength. The hydraulic machines present some advantages. 1) The harder participants push or pull and the faster they move, the greater the resistance they create. Consequently, participants can adjust the strength exercise training load. 2) Hydraulic exercise machines are designed to be used by all muscle groups. Machines exist to work the upper body, lower body, abdominals, and obliques. Therefore, participants can easily develop muscles throughout the body. 3) The hydraulic exercise machines are safer for older people to use than exercise machines of other types because the loads of the hydraulic machines disappear when participants stop moving such as pushing or pulling.

Second, training periods (30 min per day, three days a week for four weeks) in our combination exercise training are shorter than those in previous exercise training studies. Meta-analysis showed that earlier exercise training studies used long-term training periods (>24 weeks) [14]. Considering reduced costs for older people, shorter intervention studies using exercise training are also needed. Consequently, our short-term combination exercise training can offer important suggestions for methods used in the exercise training field.

Third, some previous studies showed that combination exercise training improved certain cognitive functions such as memory functions [26,27]. However, it remains unclear whether or not combination exercise training can improve cognitive functions of other types. In this study, we use diverse cognitive function measures simultaneously. Therefore, we can investigate the beneficial effects of the short-term combination exercise training on diverse cognitive functions such as executive functions, episodic memory, and processing speed.

This study investigates the beneficial effects of short-term combination exercise training on the cognitive functions in older people. If findings indicate that our short-term combination exercise training is very effective, then we will conduct future studies. For instance, assuming the validity of effects of short-term combination exercise training on diverse cognitive functions, we can conduct the same RCT for non-healthy older people such as those with dementia or depression. Additionally, we will investigate the beneficial effects of our combination exercise training on brain functions and brain structures using neuroimaging techniques such as magnetic resonance imaging.

We discuss the risks of this study. As there are no known side effects and there have not been any reports of adverse reactions to the combination exercise program for older people, we do not anticipate that any participants will be exposed to any unnecessary risks. However, there are risks of using the strength training machines. To reduce these risks, we conduct the combination exercise training with the presence of professional trainers, who have all been approved for the study by the Ethics Committee and have worked for more than two years as a trainer using the combination exercise training.

There are some limitations in this study. First, the intervention period of this study is shorter than that of the previous studies. The short-term intervention such as four weeks is one of advantages or strong points of this study. The previous study for older people demonstrated that four weeks’ intervention period could be enough to improve some cognitive functions (the main purpose of this study) [13]. However, it may not be long enough for older people to gain cardiovascular health, to control weights and to get into the habit of exercise. Gaining cardiovascular health or controlling weight is not important for our participants because we recruit healthy older people who are not suffering from obesity and hypertension. The habit of exercise would keep cognitive functions and mental health in later life. In future study, it will be necessary to investigate whether or not the short-term intervention would facilitate older people gaining cardiovascular health or getting into the habit of exercise.

Second, we do not use an active control group who participates in other types of exercise programs. The reasons why we use the wait-list group are that 1) previous studies showed no difference exists in cognitive or functional improvement between the stretch exercise training group (active control group) and non-exercise control group (control group) [36] and 2) using the wait-list group has the advantage that all participants can experience the combination exercise training. From a study design point of view, it would be better than using the active control group. This is the first study to demonstrate the beneficial effects of the combination exercise training on the cognitive functions. If we find the combination exercise training to be effective for older people, we should conduct new intervention studies that compare the combination exercise training to other exercise training or other cognitive training.

We should discuss the generalizability of this study because this study is a single center study (in Sendai city, Japan) using very healthy older people. The protocol of the combination exercise training uses simple hydraulic exercise machines and does not depend on language ability or Japanese language. Thus, we assume that the combination exercise can be applied to other healthy older people in Japan and would be available to everyone around the world. As we mentioned before, there are no known side effects and there have not been any reports of adverse reactions to the combination exercise program. If people who have low IQ, any CNS disease or cognitive impairment participate in the combination exercise training, the chance of an accident may increase. In that case, we should conduct the combination exercise training with expert help (for example, a medical doctor, or psychologist).

It is important to discuss the possibility of the ceiling effect in cognitive measures. Because we will recruit very healthy older people (please see the Inclusion and Exclusion Criteria section), there would be a possibility that the scores of cognitive functions in participants before the intervention are close to the maximum or the highest scores. Thus, the short-term intervention would not lead to improvement in cognitive functions of the intervention group compared to that of the control group. However, we measure a wide range of cognitive functions and use standardized cognitive measures. Moreover, our previous intervention study using video games for healthy older people [13] showed improvement of cognitive function after the four weeks’ cognitive intervention. For that reason, we would reduce the possibility of the ceiling effect in this study.

In summary, this report is the first of a study assessing the beneficial effects of short-term combination exercise on diverse cognitive functions in older people. Our study is designed to provide sufficient evidence of the effectiveness of short-term combination exercise. Given that most cognitive functions decrease with age [56] and that these functions are correlated strongly with daily life activities [6,7,57], our results can elucidate the effects of exercise training for older people.

## Trial status

Recruitment of participants, beginning in May 2012, is expected to end in January 2013. Patient recruitment is ongoing.

## Abbreviations

ADAS: Alzheimer Disease Assessment Scale; ANCOVA: Analysis of covariance; CFT: Category Fluency Task; Cd: Digit symbol coding; CONSORT: Consolidated Standards of Reporting Trials; D-CAT: Digit cancellation task; DS-B: Digit span backward; DS-F: Digit span forward; FAB: Frontal Assessment Battery; FS-N: First and second names; IQ: Intelligence Quotient; JART: Japanese reading test; LFT: Letter Fluency Task; LM: Logical Memory; MMSE: Mini Mental Status Examination; QOL: Quality of life; RCT: Randomized controlled trial; RBMT: Rivermead Behavioural Memory Test; SPSS: Statistical Package for the Social Sciences; SS: Symbol Search; ST: Stroop Test; UMIN: University Hospital Medical Information Network; VFT: Verbal fluency task; WAIS-III: Wechsler Adult Intelligence Scale-third edition; WMS-R: Wechsler Memory Scale-revised.
